### Sample size

The power analysis is based on previous results of appropriate antibiotic use on length of stay as described at ‘background’ [6,7]. In a simulation study based on the stepped wedge design, with nine hospitals each contributing 180 patients with a suspected infection, we estimated the power to approximate 80% to demonstrate a significant reduction of 13% in length of stay, assuming that the intraclass correlation coefficient does not exceed 0.20. With each hospital contributing 180 patients with a suspected infection, the total sample size will be 1620 patients. For each hospital we have determined a minimum number of patients in the baseline group and intervention group, depending on the randomization order of the hospital in the stepped wedge.

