## Background

### The need to improve antibiotic use

The increasing antimicrobial resistance rate is one of the most important health care problems at this moment. The total consumption of antibiotics is the main driving force [1,2]. The World Health Organization signalled the emergence of antimicrobial resistance (AMR), along with the steady decline in the discovery of new antimicrobials, as a major health threat for the coming decade. To help control AMR, a better use of the current agents is necessary [3]. Recent studies have shown considerable room for improvement in the two most common bacterial infections: respiratory and urinary tract infections [4,5]. An important question is how to achieve such an improvement.

Previous studies have shown that appropriate antibiotic use is not only of great importance to curb antimicrobial resistance, but also has a short-term consequence. The evaluation of antibiotic treatment for urinary tract infections in hospitals showed an inverse relationship between the proportion of appropriate antibiotic use in a patient and length of stay (LOS). Prescribing therapy in accordance with local hospital guidelines was associated with a shorter LOS (7.3 days vs. 8.7 days; P = 0.024) [6]. Recently a similar inverse relationship has been shown between appropriate antibiotic use in treatment of all bacterial infections in the hospital and LOS, with a reduction of 13% in LOS with appropriate use. [*Abstract poster:* Quality Indicators for Monitoring Appropriate Antibiotic Use in Hospitals: an Important Tool for Antibiotic Stewardship. K-325. *54th Interscience Conference on Antimicrobial Agents and Chemotherapy, September 5 -9, 2014, Washington DC*].

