### Phase 2: cluster randomized clinical trial to evaluate the AB-checklist

#### Study design and setting

The (cost-) effectiveness of introducing the antibiotic checklist will be studied in a controlled, multicentre, prospective study using a stepped wedge design, comparing outcomes before and after implementation of the checklist while accounting for potential confounders [14].

The checklist will be introduced in nine hospitals over four time periods, during a total study period of eleven months (Figure 2). The aim is to include at least 810 patients in the period before- (the baseline group), and at least 810 patients with a completed checklist in the period after checklist introduction (intervention group). During the transition period implementation activities will be started and no patients will be included. This period runs from one month before introduction of the checklist to one week after introduction. Since compliance to the checklist will not be 100%, we will also collect data concerning the LOS from the patients in whom the checklist should have been but was not completed during the period after checklist introduction (the spill over group).

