#### Economic evaluation

The key question for the economic evaluation is whether the benefits of using the checklist, which will likely include reduced antibiotic use, reduced length of stay and associated costs, justify the costs associated with implementation activities as well as daily use of the checklist. For reasons of feasibility, the cost analysis will only include a few main cost drivers of health care utilization, namely LOS on a general or ICU ward and antibiotic use. Unit costs for health care utilization will be estimated according to the Dutch guideline on (unit) costing in health care [18]. LOS and ICU stay will be valued based on the guideline prices. Furthermore, we will compare the total antibiotic use in days per antibiotic class in the baseline and the intervention group. Antibiotic costs will not be valued because the benefits become more evident in terms of reduced quantities rather than their particular costs. Implementation costs will be divided in non-recurring and recurring costs. Non-recurring costs are related to our study, such as costs of the development of the materials, the implementation strategy and costs of evaluation of the implementation. Recurring costs are the costs of accomplishment of the implementation strategy. The primary analysis is a cost-effectiveness analysis, with the incremental cost-effectiveness ratio expressed as the implementation related costs per reduction of length of stay in days. As we hypothesize that an effective implementation of the checklist will result in reduced health care use and thus lower costs, we will also perform a cost-benefit analysis, evaluating whether the implementation costs are offset by this cost reduction (costs of implementation < health care cost reduction). Robustness of the results for uncertainty in the assumptions will be evaluated in sensitivity analyses, including estimates of unit costs and volume of implementation activities (considering less activities will be needed if checklists become part of standard care). In a budget impact analysis results from the economic evaluation will be extrapolated to the national level to estimate the total clinical and budget impact in terms of health benefits, reduction in antibiotic use, and associated economic impact on the health care budget per annum for the Netherlands. The budget impact analysis will be performed according to the criteria provided by Mauskopf et al. [19], from a societal perspective as well as from the health insurance and/or national health care budgeting framework perspective. We will evaluate the impact of varying implementation rates, comparing care as usual (0% implementation), potential impact (100% implementation), and the probable rates of 85% and 50% implementation.

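### The 13% behind the stated 80% power is an association with appropriate antibiotic use; the intention-to-treat effect of introducing the checklist should be smaller, and its power below 80%

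*Protocol article*

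**What the plan says.** All references are to the protocol article.

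- *Sample size*: "The power analysis is based on previous results of appropriate antibiotic use on length of stay". The simulation is described "with nine hospitals each contributing 180 patients with a suspected infection", 1620 in total, "assuming that the intraclass correlation coefficient does not exceed 0.20". The stated result is "we estimated the power to approximate 80% to demonstrate a significant reduction of 13% in length of stay".
- *The need to improve antibiotic use* (Background) gives the origin of the figure: an inverse relationship between appropriate use and LOS across bacterial infections, "with a reduction of 13% in LOS with appropriate use".
- *Effect evaluation* lists two comparisons for LOS. The first, for the overall effect, sets baseline against everyone eligible after introduction (intervention group plus spill-over group) and is called intention to treat. The second leaves out the spill-over group, is called per protocol, and is described as the theoretical effect.
- *Study design and setting*: "Since compliance to the checklist will not be 100" per cent, LOS is also collected for eligible patients whose checklist was not completed. The post-introduction target of 810 counts completed checklists only.
- *Economic evaluation*: the budget impact analysis, extrapolated to national level, considers among others "the probable rates of 85% and 50% implementation".

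**The concern.** The effect size and the analysis answer different questions. The 13% compares LOS by how appropriately patients were treated. The ITT analysis compares all eligible patients before and after a checklist is introduced. If the checklist shortens stay by making treatment more appropriate, which is the plan's rationale, the ITT effect is only a part of the 13%. The part depends on how many patients get a completed checklist, how far the introduction improves care in the others, and how much care was already appropriate beforehand. The sample size section mentions none of these.

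At stake is the reading of a null result. It could be taken to show that the checklist does not work, when the trial had less than the stated power for the effect its own rationale predicts. The article plans to collect only LOS and confounders in the spill-over group (*Assessments*), so appropriateness in the full ITT population could not be used afterwards to explain such a result.

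**Working it through.** **The plan's own figure.** 9 × 180 = 1620 and 810 + 810 = 1620 both agree. The 80% cannot be checked independently, because the article gives no standard deviation (SD) for LOS and no significance level for the power calculation. It is attainable: in stepped-wedge calculations under two assumed layouts (the design figure is not shown), 80% results if the SD of log LOS is about 0.56 to 0.62 with period effects, or 0.92 to 1.02 without. I therefore take 80% at 13% as given and ask what it implies for smaller effects.

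**Inputs**
- From the article: 13%, 80%, 810 per group.
- Assumed: log scale, two-sided 5% level, normal approximation.
- Completion c: 85% and 50%, borrowed from the budget impact analysis as illustrations only.
- Share s of the full effect reaching spill-over patients: assumed 0 or 0.5.
- Every completed checklist is assumed to deliver the full 13%, which is generous.

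**Formulas**
- Implied standard error: SE = |ln 0.87| / (1.960 + 0.842) = 0.1393 / 2.802 = 0.0497.
- ITT effect: e = 0.13 × [c + (1 − c) × s].
- Power = Φ(|ln(1 − e)| / SE − 1.96).
- With spill-over patients counted, the post-introduction group is 810/c and SE is multiplied by √[(1 + c)/2]. This factor is 0.962 at c = 0.85 (953 patients) and 0.866 at c = 0.50 (1620 patients).

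**Results**

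| Completion c | Spill-over share s | ITT effect | Power, N = 1620 | Power, spill-over counted |
|---|---|---|---|---|
| 100% | – | 13.0% | 80% | 80% |
| 85% | 0 | 11.1% | 65% | 69% |
| 85% | 0.5 | 12.0% | 73% | 76% |
| 50% | 0 | 6.5% | 27% | 35% |
| 50% | 0.5 | 9.75% | 54% | 66% |

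Worked line for 85% and s = 0: e = 0.13 × 0.85 = 0.1105; |ln 0.8895| = 0.1171; 0.1171/0.0497 = 2.356; Φ(2.356 − 1.96) = Φ(0.396) = 0.65. With spill-over counted: 2.356/0.962 = 2.449; Φ(0.489) = 0.69.

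**Sensitivity.** The zero-benefit rows were repeated in a stepped-wedge model with intraclass correlations (ICC) of 0.01, 0.05 and 0.20, two layouts, and with and without period effects. The fixed-N figures did not change; the spill-over-counted figure was about 69% at 85% completion and 34 to 36% at 50%. They are stable because the SD is recalibrated to 80% at 13% each time.

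**Smallest detectable ITT reduction at 80% power**, on the same calibration: 1 − exp(−2.802 × SE). This is 13.0% at N = 1620, 12.5% with spill-over counted at 85% completion (SE 0.0478), and 11.4% at 50% (SE 0.0430). The extra patients lower the detectable effect by less than incomplete completion lowers the expected one in every row of the table.

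**The case against.** **The sentence is conditional.** It claims about 80% power if LOS falls by 13%, and nothing shows that to be wrong. This stands. A reader might infer an arithmetic error; there is none. The weakness is the basis for choosing 13%.

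**The loss may be small.** The introduction includes education, feedback on baseline prescribing, reminders and supervisor involvement (Table 1), which reach the physicians treating spill-over patients too. At 85% completion, if those patients gain three-quarters of the effect, power is 77%, or 80% with spill-over counted. The 85% and 50% are national implementation scenarios, not forecasts of compliance in this trial. This stands as well. A reader might infer that power is far below 80%; the article does not establish that. Still lower figures, about 27% for a 50-point rise in appropriate use or 12% for a 30-point rise, rest on rises that appear nowhere in the document.

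**The 13% may not be an all-or-nothing contrast.** The Background speaks, for the urinary tract study, of the proportion of appropriate use within a patient, and the endpoints include a sum score. The source is not at hand, so strict proportional dilution from 0% to 100% appropriate care is an assumption. The direction does not depend on it: an association between better and worse treated patients is not the effect of offering a checklist to all.

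**The 810 completed checklists against 1620 simulated patients.** This mismatch does not cost power. Both targets are minimums, and spill-over patients add to the ITT analysis.

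**The ICC ceiling.** A reader might infer that 0.20 is not the worst case. That depends on which variance is held fixed. For an assumed 2/2/2/3 layout with period effects, the standard error per unit SD falls from 0.0855 at ICC 0.05 to 0.0805 at 0.20 with total variance fixed, but rises from 0.0878 to 0.0900 with residual variance fixed. The article does not say which applied, and it does not show the layout. No criticism of the ICC follows.

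**Conclusion.** The point holds as a fault in the basis of the effect size and should be fixed. The stated power rests on an association with appropriate use, while the first-listed analysis of the primary endpoint (the article does not literally call it primary) measures the effect of introduction in all eligible patients. With compliance expected to be incomplete, and some baseline care presumably already appropriate, the expected ITT effect is below 13% and power for it below 80%.

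The size is illustrative. The mildest scenario with no spill-over benefit (85% completion) costs 11 to 15 percentage points; half the benefit in spill-over patients reduces that to 4 to 7. At 50% completion with no benefit, power is 27 to 35%. All of this assumes that 80% at 13% is correct, a log scale, a two-sided 5% level, and the full 13% from every completed checklist. Care already appropriate at baseline lowers power further, by an amount the article does not allow one to compute.

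**What to change.** Keep the sample size. Then:

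1. Re-run the existing simulation for the ITT contrast and population, with spill-over patients counted.
2. State the assumptions for compliance, benefit in spill-over patients and rise in appropriate use, and derive the ITT effect from them.
3. Restate the power over a range of these assumptions, and give the smallest ITT reduction detectable with 80% power.
4. Describe 13% as an optimistic effect that assumes full conversion to appropriate use.

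The cost is a repeat of a simulation that already exists and a few sentences of text. No patient, endpoint or analysis changes. The downside is a less favourable stated power.

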### Analysis

#### Effect evaluation

We will use mixed linear models to analyse the overall effect of the introduction of the checklist on length of stay. Therefore we will evaluate differences between baseline (before introduction of the checklist) and intervention plus spill over (after introduction of the checklist) (intention to treat analysis). We will also determine the theoretical effect of the checklist on LOS by evaluating differences between baseline and intervention data without the spill over data (per protocol analysis). Differences between the baseline data and the intervention data for secondary outcomes will also be evaluated with mixed linear models. For dichotomous outcomes (mortality), the comparison will be evaluated with a similar approach, using generalized estimating equation models. These mixed models account for within-cluster dependencies, and allow adjustment for possible confounders. To assess whether differences between these groups may be explained by confounding patient characteristics, we will first test with multivariate multilevel (linear mixed) analyses if these variables have a significant effect (p < 0.05) on the outcomes. Hereafter, we will compute the estimate of the total causal effect of checklist implementation on the outcomes before and after adjusting for a significant variable. If the estimate varies 10% or more, possible confounding is present and in that case we will adjust for this variable.

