**Flowchart of the included patient in our study.**

### Primary and secondary endpoints

The primary endpoint is length of hospital stay in days. LOS in community-acquired infections will be defined as the number of days between admission and discharge. In hospital-acquired infections LOS will be defined as the number of days between start of antibiotic treatment and discharge. Secondary endpoints are appropriate antibiotic treatment according to the generic QIs (yes/no per QI and sum score of all QIs) [6], admission to and duration of ICU stay in days, readmission within 30 days, mortality in the hospital and in the first 30 days after discharge, total antibiotic use, costs of hospital stay and costs associated with implementation.

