### Assessments

For patient outcome we will collect data concerning the LOS, admission to and duration of ICU stay, readmission within 30 days and mortality in hospital or within 30 days after discharge for the baseline group and the intervention group. Furthermore we will collect data for possible confounders of patient’s outcome, namely age, sex, community-or hospital acquired infection, Charlson comorbidity index [15,16], use of antibiotics during the previous 30 days, and clinical condition as assessed by the Modified Early Warning System [17]. To calculate QI performance we will collect data concerning the number of taken blood cultures including its results, the number of taken cultures of suspected sides of infection including its results, antibiotic use including dose, interval and duration of treatment in days, the (suspected) type of infection and relevant laboratory parameters. For the spill over group, we will only collect data concerning the LOS and the possible confounders.

Antibiotics included in the study belong to group J01 (antimicrobials for systemic use) of the Anatomic Therapeutic Chemical (ATC) classification system. When multiple antibiotics are prescribed to one patient, all antibiotics will be registered. Antiviral therapy, medication for tuberculosis, antibiotics used for non-systemic selective intestinal decontamination and antibiotics used as pro-kinetics will be excluded.

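### The stepped-wedge effect models name no calendar-time term, so a shared trend in length of stay, and season depending on its phase, would bias the checklist effect

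*Protocol article*

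**What the plan says.** The design section of the protocol article describes a stepped wedge "comparing outcomes before and after implementation of the checklist while accounting for potential confounders". The schedule is stated as follows: "The checklist will be introduced in nine hospitals over four time periods, during a total study period of eleven months". Each hospital has a transition window without inclusion: "This period runs from one month before introduction of the checklist to one week after introduction". The sample size section refers to the randomised order of the hospitals.

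On the endpoint: "The primary endpoint is length of hospital stay in days". Under Effect evaluation: "We will use mixed linear models to analyse the overall effect of the introduction of the checklist on length of stay". The intention-to-treat contrast is then given: "we will evaluate differences between baseline (before introduction of the checklist) and intervention plus spill over (after introduction of the checklist". The per-protocol analysis leaves out the spill-over patients, and secondary outcomes are compared between baseline and intervention data in the same way, with GEE for dichotomous outcomes.

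The same section says that the models deal with within-cluster dependence and permit adjustment for possible confounders. It treats these as patient characteristics and admits one only if it is significant at p < 0.05 and shifts the estimate by 10% or more. The Assessments section lists the candidates: "namely age, sex, community-or hospital acquired infection, Charlson comorbidity index", followed by antibiotic use in the previous 30 days and the early-warning score. No time variable is named in any of these places.

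**The concern.** Within a hospital, checklist exposure and calendar time move together by design. Randomising the order of introduction protects against a common trend only if hospitals that have and have not yet introduced the checklist are compared at the same calendar time. In the model, that requires a time term. With a hospital random effect alone, the estimate is essentially a pooled before-after difference, and most of the benefit of the staggered order is lost.

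A general shortening of stay, bed pressure or other stewardship activity would then be read in part as a checklist effect. The study lasts eleven months, so seasons need not balance, and the Background names respiratory infection among the two most common infections. The secondary outcomes are exposed in the same way. The reduction in length of stay is also the denominator of the cost-effectiveness ratio, so a bias would carry into the economic results.

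**Working it through.** **The plan's own figures.** 9 × 180 = 1620 = 2 × 810, which agrees. The power of about 80% for a 13% reduction at ICC up to 0.20 can be neither reproduced nor refuted: the document gives no SD, alpha or simulated model, and the figure with the step layout is not shown.

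**Inputs from the document.** 9 hospitals, 180 patients each, 11 months, transition from 1 month before to 1 week (0.23 month) after introduction, ICC up to 0.20.

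**Assumed.** Introduction at months 3/5/7/9 in 2/2/2/3 hospitals; even recruitment outside the transition; analysis of log length of stay with SD 0.5, 0.7 or 0.9; ICC 0.05 or 0.20; two-sided 5% test; no true effect; a steady decline of 5% or 10% per year.

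**Step 1, time gap.** For introduction at month c, the mean baseline date is (c − 1)/2 and the mean post-introduction date is (c + 0.23 + 11)/2. The difference is (11 + 1 + 0.23)/2 = 6.1 months, whatever c is. Generalised least squares with a hospital random intercept and no time term gives an effective gap of 6.0 months (ICC 0.05) to 6.1 months (ICC 0.20).

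**Step 2, bias.** Bias on the log scale = ln(1 − yearly decline)/12 × gap.
- 5% per year: ln(0.95)/12 × 6.08 = −0.026, a false reduction of about 2.6% (2.5% at ICC 0.05).
- 10% per year: ln(0.90)/12 × 6.08 = −0.053, a false reduction of about 5.2% (5.1% at ICC 0.05).

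**Step 3, standard error.** A hand check uses within-hospital information only: variance = SD² × (1 − ICC) / Σ(n₀n₁/180). Each hospital recruits for 11 − 1.23 = 9.77 months. The terms n₀n₁/180 are 29.3, 43.5, 42.7 and 26.7 for months 3, 5, 7 and 9. Their sum is 2 × 29.3 + 2 × 43.5 + 2 × 42.7 + 3 × 26.7 = 311. At SD 0.7 and ICC 0.20, √(0.49 × 0.8/311) = 0.0355; full least squares gives 0.0353.

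**Step 4, type I error.** Φ(−1.96 + z) + Φ(−1.96 − z), with z = |bias|/SE. At SD 0.7 and ICC 0.20, z = 0.026/0.0353 = 0.74 gives 11%, and z = 0.053/0.0353 = 1.51 gives 33%. The ranges below run over ICC 0.05–0.20.

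| SD of log stay | 5% per year | 10% per year |
|---|---|---|
| 0.5 | 16–18% | 49–56% |
| 0.7 | 10–11% | 28–33% |
| 0.9 | 8–9% | 19–22% |

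**Step 5, season.** With a ±5% yearly cycle, the bias is up to about 6% at the worst phase. At SD 0.7 the type I error is 35–41% at the worst phase, 20–23% averaged over phase, and about 5% at favourable phases.

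**Step 6, with period effects.** Indicators for the steps leave a bias below 0.5% for these trends, and a linear time term removes it. At ICC 0.20 the standard error rises by a factor of about 1.6–1.8 over three layouts (four steps with 2,2,2,3 or 3,2,2,2 hospitals; three steps with 3,3,3).

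**Step 7, power.** On the scale of SD relative to mean stay, at ICC 0.20, about 80% power for 13% needs a ratio of about 0.88–0.92 without a time term and about 0.52–0.54 with one. If the stated 80% came from a model without time, the same design would have about 35–40% with it.

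**The case against.** The strongest reply is that silence is not exclusion. The quoted contrast mainly says which patients enter the intention-to-treat comparison. The article condenses a fuller plan and never writes out the model. The confounder list concerns patient-level data to be collected, whereas period is a design factor and can be derived from dates already held. The design section speaks generally of potential confounders, and the simulation was based on the stepped wedge.

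Part of this stands. A reader might infer that the plan rules out a time term; no sentence does so, and an unseen analysis plan could add one. The gap that remains is still more than missing detail. The article states the contrast, what the models handle, the type of confounder and the entry rule, and time is in none of them. An analysis that follows this text omits time. If time were instead treated as one of the possible confounders, its inclusion would depend on the data.

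The magnitudes rest on assumed inputs, which is also fair. The document reports length of stay in days and mentions no log scale, and minimum numbers per hospital depend on the order of introduction, so even recruitment is not given. For a common trend, the direction of the bias does not depend on these choices.

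Two further readings go too far. One is that any seasonal change is credited to the checklist: a seasonal pattern can partly balance over the staggered steps, and measured case-mix shifts can be adjusted for. The other is that the 80% power was computed without time effects: the document does not say which model was simulated.

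**Conclusion.** The point holds as a defect in the stated analysis. As written, it gives in effect a pooled before-after estimate in which a shared trend is not separated from the checklist effect. The illustrative bias of 2.5–5% is about a fifth to two fifths of the 13% target (2.5/13 = 0.19; 5/13 = 0.38). The type I error of 8–56% spans both drift rates and SD 0.9 to 0.5. These sizes depend on the assumed layout, SD, scale and drift, none of which the document gives. The dependence on a common trend follows from the design alone. Because the validity of the primary test is affected, this should be settled before the analysis. The power consequence is conditional on what the simulation contained.

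**What to change.** Pre-specify calendar period (step or month) as a fixed effect in every effect model: mixed linear and GEE, primary and secondary outcomes, intention-to-treat and per-protocol. Keep it in regardless of the p < 0.05 and 10% change rule, which should apply to patient characteristics only. Retain the hospital random effect in the mixed models. A hospital-by-period random effect may be a sensitivity analysis; with nine hospitals it is debatable as a requirement.

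State whether the power simulation included period effects. If it did not, re-run it with them and restate the power.

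No new data are needed, since dates are already required to classify patients as before or after introduction. The cost is in precision: a standard error about 1.6–1.8 times larger under the layouts tried, and hence a less favourable power figure if the simulation left time out.

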#### Validation and process evaluation

We will evaluate the physicians’ compliance with the checklist. Firstly we will check whether the ticks in the completed checklists are in accordance with the performance in clinical practice. Secondly we will determine the percentage of eligible patients for whom the checklist has been used after checklist introduction. The number of patients in whom the checklist was actually used (the intervention group) will be divided by the number of patients in whom it should have been used (the intervention plus the spill over group).

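### The per-protocol estimate of the checklist's effect on LOS drops non-completers after introduction but not at baseline, so selection by the physician can appear as, or hide, an effect

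*Protocol article*

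**What the plan says.** Study design and setting divides eligible patients after introduction by whether the form was completed. The intervention group is "at least 810 patients with a completed checklist in the period after checklist introduction (intervention group"); the spill over group consists of "patients in whom the checklist should have been but was not completed". Eligible patients states that everyone meeting the criteria is included, with or without a completed form, so the baseline group is not selected on completion.

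Effect evaluation then plans two contrasts on LOS:

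- First, for the overall effect, to "evaluate differences between baseline (before introduction of the checklist) and intervention plus spill over (after introduction of the checklist) (intention to treat analysis").
- Second, "We will also determine the theoretical effect of the checklist on LOS". The method named for this second estimate is "evaluating differences between baseline and intervention data without the spill over data (per protocol analysis").

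Both may be adjusted for patient characteristics. A variable enters only if it is significant at p < 0.05 and its inclusion moves the estimate by 10% or more. Assessments lists six: age, sex, community- or hospital-acquired infection, Charlson index, antibiotics in the previous 30 days, and the Modified Early Warning System. It adds: "For the spill over group, we will only collect data concerning the LOS and the possible confounders". Validation and process evaluation defines compliance as the number of patients with a used checklist "divided by the number of patients in whom it should have been used".

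**The concern.** The second contrast compares two populations that differ by construction. The post-introduction side holds only patients whose physician completed the form. The baseline side holds every eligible patient, including those for whom the same physicians would not have completed it. If completion is related to how long a patient would stay anyway, for instance through severity, an atypical presentation, workload or the prescriber's habits, that relation enters the estimate as though the checklist had caused it.

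At stake is how a figure on the primary endpoint is read. The protocol gives it a causal label. It could suggest a benefit that is not there or mask one that is.

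**Working it through.** **The plan's own figures.** 9 hospitals × 180 patients = 1620 = 810 + 810, so the Sample size section and the two group minima agree. The protocol gives no figure for the per-protocol contrast and no spread for LOS. The check below needs neither.

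**Inputs.**

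- Completion rate c: Study design and setting says only that it will be below 100%. I borrow 50% and 85% from the budget impact scenarios under Economic evaluation, as an assumption.
- r, the mean LOS of completers divided by that of non-completers when the checklist does nothing: not in the document; 0.9 and 0.8 are assumed. If adjustment removes part of the gap, r is what remains.
- Planned effect: 13% reduction (Sample size).

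**Step 1: bias with no checklist effect.** Set the non-completers' mean LOS to 1.

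- Baseline mean: cr + (1 − c)
- Post-introduction mean, intention to treat: cr + (1 − c), so the change is 0
- Post-introduction mean, per protocol: r, so the change is r / [cr + (1 − c)] − 1

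| c | r | Calculation | Apparent per-protocol change |
|---|---|---|---|
| 0.85 | 0.9 | 0.9 / 0.915 − 1 | −1.6% |
| 0.85 | 0.8 | 0.8 / 0.83 − 1 | −3.6% |
| 0.50 | 0.9 | 0.9 / 0.95 − 1 | −5.3% |
| 0.50 | 0.8 | 0.8 / 0.9 − 1 | −11.1% |

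**Step 2: what would imitate the planned effect.** Setting the change to −13% gives r = 0.87(1 − c) / (1 − 0.87c). At c = 0.50 this is 0.435 / 0.565 = 0.77; at c = 0.85 it is 0.1305 / 0.2605 = 0.50.

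**Step 3: the other direction.** If completers would stay 20% longer (r = 1.2) at c = 0.50, the factor is 1.2 / 1.1 = 1.091. A true 13% reduction would then appear as 1 − 0.87 × 1.091 = 5.1%.

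**Step 4: check by simulation.** Nine hospitals, four introduction steps (2, 2, 2, 3), five periods, 36 baseline patients and 36/c post-introduction patients per hospital and period, log-LOS SD 0.5 and intraclass correlation 0.05 (layout, SD and correlation assumed), hospital and period effects in the model, no covariates, no checklist effect, 500 runs each.

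| c | r | Per protocol: estimate, false positives | Intention to treat: estimate, false positives |
|---|---|---|---|
| 0.85 | 0.9 | −1.5%, 6% | +0.1%, 4% |
| 0.85 | 0.8 | −3.1%, 11% | +0.2%, 4% |
| 0.50 | 0.9 | −4.8%, 22% | +0.2%, 6% |
| 0.50 | 0.8 | −10.8%, 72% | −0.1%, 4% |

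With r = 1 both analyses were unbiased, with 4% to 6% false positives.

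**Step 5: intention-to-treat effect divided by compliance.** If introduction leaves non-completers untouched, a 13% effect in completers at c = 0.6 gives 0.6 × 13% = 7.8%, and 7.8% / 0.6 = 13%. If non-completers gain half of it (6.5%, assumed), intention to treat is 7.8% + 0.4 × 6.5% = 10.4%, and 10.4% / 0.6 = 17.3%. The ratio then overstates the effect by 4.3 points.

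**The case against.** The strongest reply is that this is a supplementary analysis. Intention to treat comes first and carries the overall effect, and post-randomisation selection is a known limit of any per-protocol analysis. This stands. A reader might infer that the trial's conclusion on LOS is unsafe. The documents do not support that, because the first contrast keeps completers and non-completers together. Nor does 810 + 810 = 1620 show that the per-protocol set is the principal one: Effect evaluation does not say so.

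Second, adjustment is planned, and the Modified Early Warning System measures part of what makes a patient very sick. This stands in part. The bias that matters is what remains after adjustment, so the figures above are unadjusted ones. But covariates that each move the estimate by less than 10% stay out, whatever they do jointly, and all six describe the patient. None describes the prescriber, the ward or the circumstances of prescribing.

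Third, nothing in the protocol shows that completion is related to LOS, and both c and r are assumed. That is correct. A reader might infer that the contrast will produce a spurious 13%. At 85% completion this would need completers to stay half as long as non-completers, and even at 50% they would have to stay 23% shorter. These are extreme cases.

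Fourth, dividing intention to treat by compliance might be taken as the valid replacement. The protocol gives reason for doubt. The education with feedback, posters, pocket cards and supervisor involvement in Table 1 can reach prescribers whether or not they complete a form, and Step 5 shows the consequence. Weighting on the collected confounders does not escape either: like regression adjustment, it assumes no unmeasured selection.

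**Conclusion.** The point holds for the per-protocol estimate and its label. As defined, the contrast is non-randomised and cannot by itself be presented as the checklist's effect on LOS. With no true effect, before adjustment, and with completers' LOS 10% to 20% below non-completers', the spurious reduction is 1.6% to 3.6% at 85% completion and 5.3% to 11.1% at 50%. It is thus small when completion is high and selection mild, and close to the planned 13% only when completion is low and selection strong. The sign is not known. These sizes rest on assumed completion rates and LOS gaps. That non-completers leave one side only follows from the protocol's own definitions. The intention-to-treat result on LOS is not in question.

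**What to change.** In Effect evaluation:

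1. Describe the per-protocol contrast as non-randomised and descriptive, remove the label of theoretical effect, and state that conclusions on LOS come from the intention-to-treat analysis.
2. Compare completers with the spill over group on LOS and the collected confounders. Weight completers by the inverse probability of completion given all six confounders, without the p < 0.05 and 10% screen, so that they represent all eligible post-introduction patients. State that unmeasured selection may remain.
3. Add the intention-to-treat effect divided by compliance, with a bootstrap or two-stage interval, as a sensitivity estimate only. State that it assumes introduction has no effect on non-completers, and that it overstates the effect if the Table 1 activities also improve their care.

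The cost is a change of wording, a few extra model runs and wider intervals. No new data are needed: LOS and the confounders are already to be collected in the spill over group, and compliance is already to be calculated.
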